**Patient data** includes sex, date of birth, and body mass index.**Pre-operatory data** includes the name of the surgeon, date of operation, and American Society Anesthesiologists (ASA) physical status classification system [29]. During the physician’s examination information from the patient’s medical records and the physical examination will be used to identify comorbid medical conditions (diabetes, hypertension, cardiopathy, chronic obstructive pulmonary disease, ransient ischemic attack, anticoagulant-antiplatelet therapy, and other pathologies). The Charlson comorbidity score will be calculated [29]. Preoperative grading and staging of the bladder neoplasm will be done according to standard criteria (EAU) including T-stage, G-stage, and presence of a concomitant carcinoma in situ (CIS). Preoperative therapeutic interventions, including neoadjuvant chemotherapy, palliative cystectomy, and BCG-instillation will be recorded.**Peri-operative data.** Data on the surgical procedure will be categorized according to the technique used for cystectomy (open / robotic-assisted / laparoscopic) as well as for urinary diversion (open / robotic-assisted / laparoscopic). Type of urinary diversion (ileal conduit / neobladder reconstruction / other) will be documented as well as whether there is a conversion to open surgery, and the reason for conversion. Total time of surgery as well as time taken for lymphadenectomy and urinary diversion (minutes) will be measured, in addition to milliliters of peri-operative bleeding. We will record multiple peri-operative data including nerve sparing (no / unilateral / bilateral), lymphadenectomy (not performed / bilateral external iliac nodes / bilateral presacral iliac), pelvic lymph node dissection (no / limited / standard / extended), partial prostatectomy, urethrectomy, and whether frozen section ureters (no / yes normal / CIS left / CIS right) or other frozen sections (no / normal urethra / CIS urethra / normal bundle) are performed.**Post-operative and histology data.** Post-operative staging and grading of tumors and CIS, as well as tumor histology (transitional cell carcinoma (TCC), adenocarcinoma, or other) and Gleason score [30] will be recorded. Post-operative pelvic node (total number and position) will be measured as well as the presence of prostate cancer in men. Positive margins for bladder and prostate will be measured. Number of days in hospital and readmission within 30 days post-surgery will be recoded.**Immediate (< 30 days) and late (30–90 days) post-operative complications.** In the event of a patient experiencing post-operative complications, the following characteristics will be recorded: number of complication events, time of first complication event, a description of each complication, Clavien-Dindo classification of immediate complications [31], and the date and description of treatment used. This information will be recorded both for immediate (30 days after surgery) and late (30–90 days after surgery) post-operative complications.**Follow up and outcomes.** All patients will be followed for 24 months after surgical intervention to assess multiple outcomes: mortality, tumor recurrence, continence, and sexual potency. In the event of a patient moving to another medical facility for follow-up treatment, the physician will be responsible for collecting follow-up data from them, with the patient’s consent. Follow-up data will include hospital readmission within 90 days, reoperation within 90 days, and mortality (and cause of death and autopsy data). In the event of tumor recurrence, data will be taken on date and localization of tumor recurrence, and subsequent treatment (adjuvant chemotherapy or radiation). Functional outcomes will include daytime and nighttime continence and sexual potency rates (at > 6 months and > 12 months) reported by patients to the physicians.

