
### Statistical analysis

Data will be cleaned and checked for discrepancies by a statistician before analysis. In cases of missing data, the responsible physician will be contacted and requested to check medical records and data-sheets for missing information. Characteristics of patients with missing data will be examined, and if necessary, sensitivity analysis or multiple imputation will be used to examine the effect of missing data on the results. Chi-square and students t-test will be used to assess differences in categorical and numerical data, respectively. The four main long-term outcomes of interest are recurrence-free survival, cancer-specific survival, overall survival, and functioning (continence and potency). Cox proportional regression models with 95% confidence intervals will be used to assess the risk of mortality or tumor recurrence according to the surgical technique used (open, laparoscopic, robot-assisted technique for cystectomy and/or urinary diversion). The exposure variable will be classified into different categories to also examine changes in surgery type during the operation (e.g., robot-assisted cystectomy and open surgery urinary diversion versus robot-assisted for both stages of the intervention). Logistic regression models, with adjustment for follow-up time, will be used to assess outcomes at different time points including: i) peri-operative factors (e.g., surgery time, blood loss, etc); ii) immediate post-operative factors (number of days in hospital post-operative complications etc) and; iii) long-term oncological and functional outcomes (mortality, tumor recurrence, continence and potency) up to 24 months post-surgery. Multivariable models will be used, with potential confounders selected both a-priori and on the basis of meeting the three statistical criteria for confounding (associated with the exposure, associated with the outcome, and not being on the causal pathway between exposure and outcome). Stratification and adjustment will be made according to the medical center, primary surgeon responsible for the operation and their years of medical experience, and various pre-surgery factors (tumor grading and staging, comorbidity, ASA score etc). Sample size is estimated according to a similar previous protocol [32], which is based on an overall complication percentage of 65% in the open radical cystectomy [33] with power set at 80% and alpha 5%, a sample size of 338 (2 × 169) patients is required to detect a decrease in the overall complication rate of 15%, i.e. from 65 to 50%.

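### Logistic regression is the only multivariable model named for surgery time, blood loss and hospital days, which are recorded in minutes, millilitres and days

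*Protocol article*

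**What the plan says.** All of this is in the protocol article.

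- **Model (Statistical analysis).** "Logistic regression models, with adjustment for follow-up time, will be used to assess outcomes at different time points". The list that follows has three groups. The first two are "peri-operative factors (e.g., surgery time, blood loss, etc); ii) immediate post-operative factors (number of days in hospital post-operative complications etc"; the third holds oncological and functional outcomes up to 24 months. The follow-up-time clause governs the whole list.
- **Scale of the outcomes (Variables).** Operating times are taken in minutes: the sentence on total surgery time continues "time taken for lymphadenectomy and urinary diversion (minutes) will be measured". Blood loss follows at once: "in addition to milliliters of peri-operative bleeding". For stay: "Number of days in hospital and readmission within 30 days post-surgery will be recoded".
- **Test for numerical data (Statistical analysis).** "Chi-square and students t-test will be used to assess differences in categorical and numerical data, respectively".
- **Groups compared (Aims; Strengths and relevance).** There are three techniques: open, laparoscopic and robot-assisted. The Statistical analysis section adds further categories for operations that combine techniques.

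The article names no linear, log-linear, count, ordinal or rank-based model. It gives no threshold for any of these outcomes.

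**The concern.** Technique is chosen by the surgeon, so the multivariable model, not the crude comparison, has to carry the inference. For three outcomes listed by name, the model given does not take the data in the form in which they are collected. An analyst following the text must add a step that it does not describe.

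If that step is a cut-point, precision is lost and the adjusted odds ratio depends on where the cut falls. The Background section cites less bleeding, and possibly a shorter stay, as advantages of the robotic approach. So two of the three affected outcomes are ones on which a difference between techniques is anticipated.

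The follow-up covariate raises a separate problem. Minutes of surgery and millilitres lost are final when the operation ends, and the index stay is final at discharge. Follow-up accrued later cannot explain them and may itself depend on technique or outcome.

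The t-test is a lesser matter: it compares two groups, while the registry compares at least three.

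**Working it through.** **1. The plan's own figure.** The article requires 338 patients (2 × 169) to detect 65% versus 50% complications with 80% power and alpha 5%. The two-sided pooled formula is

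n = [1.960·√(2·p̄·(1−p̄)) + 0.842·√(p₁(1−p₁) + p₂(1−p₂))]² / (p₁−p₂)².

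With p̄ = 0.575, n = [1.960·√0.48875 + 0.842·√0.4775]² / 0.15² = (1.370 + 0.582)² / 0.0225 ≈ 169.3 per group. That is 170 rounded up, and power at 169 is 79.9%. The figure reproduces. It concerns a binary outcome in two groups, so the sample size is not at issue here.

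**2. Outcome by outcome.**

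| Outcome named under logistic regression | Recorded as | Fits binary logistic regression as recorded? |
|---|---|---|
| Surgery time | minutes | No |
| Blood loss | millilitres | No |
| Days in hospital | number of days | No |
| Post-operative complications | events with description; any versus none can be derived | Yes, as any complication |
| Continence, potency | patient-reported rates | Yes |

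The misfit is confined to the first three rows.

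**3. What a cut would cost (illustration).** The article gives no standard deviations, so I assume a normal outcome, two groups of 169 and an unadjusted comparison.

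- Efficiency of a median split: 2/π = 0.637, or about 64%.
- Shift detectable with 80% power on the continuous scale: (1.960 + 0.842)·√(2/169) = 0.305 SD.
- Median split: proportions Φ(±0.305/2) = 0.561 and 0.439.
- Cut at the 75th or 90th percentile of one group: proportions 1−q and 1−Φ(z_q − 0.305).

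| Cut | Power at 169 per group | n per group for 80% |
|---|---|---|
| None (continuous) | 80% | 169 |
| Median | 61% | 267 |
| 75th percentile | 56% | 295 |
| 90th percentile | 42% | 434 |

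As a check, 169/267 = 0.633, close to 2/π. The same true difference thus has power between 42% and 61% depending only on the cut.

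**4. Pairwise t-tests in three groups.** Three independent tests at 5% would give 1 − 0.95³ = 14.3%. Pairwise tests share groups and are correlated. Simulation under the null (20,000 runs, normal data, 1000 patients in total) gives 12.4% with groups of 333/333/334 and 11.9% with 500/100/400. Both splits are assumed, because the article states no expected group sizes. A further simulation with 100 per group gave 12.3%.

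**The case against.** Several stronger readings are tempting, and the document does not support them.

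- **That dichotomisation is forced and the cuts will be picked from the data.** The text does not say binary. A cumulative-logit model is also a logistic regression and can take ordered days, minutes or millilitres without a cut-point. Nothing is said about when or how thresholds would be set, and an analysis plan not shown here could fix them in advance. This stands: the need for a cut holds for a binary model only. But no ordinal model is named either.
- **That a count of complications is put into logistic regression.** A comma seems to be missing, and the words for a number belong to days in hospital. The sample-size calculation treats complications as a rate, which suits logistic regression.
- **That the t-test will be run across three techniques without correction.** The sentence is general and follows directly on the one about patients with missing data, where a two-group comparison would be natural. Pairwise t-tests are valid in themselves, and a multiplicity rule may be left to the analysis plan. This keeps the t-test a secondary point; the 12% describes one possible use.
- **That skewness invalidates the t-test.** The article gives no distributions. With about 1000 patients planned, moderate skew is a limited threat to a comparison of means.
- **That follow-up adjustment biases the results.** No bias is shown. The clause makes sense for the 24-month outcomes, and its extension to the others may be loose drafting.

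The assignment itself survives: this is a named model attached to named outcomes, not a detail left out by condensation.

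**Conclusion.** The point holds for surgery time, blood loss and days in hospital: the only multivariable model stated for them does not fit them as recorded, and its follow-up covariate has no meaning for them. Severity is moderate. The article's four main long-term outcomes are recurrence-free, cancer-specific and overall survival, and functioning. The survival outcomes have Cox models, and continence and potency suit logistic regression. The sample size is unaffected.

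The 64% and the power losses assume normality and a cut that the plan does not state. The family-wise error of about 12% assumes three ungated, uncorrected pairwise tests. These figures show what is at risk; they are not estimates of an error already made.

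**What to change.** In the Statistical analysis section:

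1. Analyse surgery time and blood loss by linear regression, on the log scale or with robust standard errors if skewed, using the same confounders.
2. Analyse hospital days by a log-linear, gamma or negative binomial model, using the same confounders.
3. Keep logistic regression for binary outcomes: any complication, readmission, continence and potency.
4. Remove the follow-up-time covariate for intra-operative and index-stay outcomes.
5. For unadjusted comparisons of numerical data across techniques, run a global test first (one-way ANOVA or Kruskal-Wallis), then pairwise contrasts. With exactly three groups, ANOVA as a gate before the pairwise t-tests already controls the family-wise error. If combined-technique categories bring the number above three, add a multiplicity correction.

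The cost is analysis wording only. The data are already collected on the scales these models need, and no extra patients or variables are required.

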## Discussion

### Summary

The current protocol aims to contribute additional data to the field concerning the short- and long-term outcomes of different radical cystectomy surgical techniques for patients with bladder cancer. Similar registries are ongoing, for example in the Netherlands [32].

### Limitations

The main limitation of the study design is that the treatment arms are not randomized. Clinical reasoning behind treatment choice may affect conclusions, although the extensive data collection on numerous potentially relevant factors will allow us to adjust for potential confounders. There is some value of comparative-effectiveness trials such as these, because thereare a complex range of factors and decision making by both physicians and patients that affect their choice of surgical technique, which cannot be assessed in RCTs.

### Strengths and relevance

Despite the lack of randomization, there are several advantages of the current protocol. The current literature is largely based on non-randomized, retrospective analysis of clinical data, but our protocol was designed prospectively and will include a much larger sample size than the currently available studies. The multicenter design also provides some variation to the data, with 28 clinics all across Italy providing data, thus minimizing selection bias. Multiple surgeons in multiple clinics will perform the different surgical techniques on diverse groups of patients (different regions of the country, socioeconomic groups, rural and urban population etc), which will increase generalizability of the results. Though most studies compare two surgical techniques, we will compare three types (open, laparoscopic, and robot-assisted). Another novel aspect is that we will perform analysis that accounts also for change in technique during surgery (e.g., robotic-assisted cystectomy plus open urinary diversion surgery versus robotic-assisted surgery for both parts of the operation). Importantly, we have planned a long follow-up of 24 months that will allow us to examine both the short- and long-term outcomes in patients. A large proportion of the current evidence focuses on short-term outcomes and data is sparse on patients’ functional outcomes such as continence and potency, but we have included up to two-years of follow-up on multiple factors, including survival, functioning, and oncological outcomes, thus providing a more comprehensive picture.

## Data Availability

Data sharing is not applicable to this article as no datasets were generated or analysed during the current study.

## Abbreviations

ASA: American Society Anesthesiologists
BCG: Bacillus Calmette-Guerin
CIS: Concomitant carcinoma in situ
EAU: European Association of Urology
RCT: Randomized control trial
TCC: Transitional cell carcinoma
